### Primärer Endpunkt:

Die Sicherheit als primärer Endpunkt wird durch klinische Untersuchung der okulären Entzündung (Spaltlampe, Funduskopie, Angiographie, Perimetrie oder Elektrophysiologie) beurteilt. Systemische Sicherheit wird durch Vitalparameter, routinemäßige klinische Chemie (einschließlich CRP, BSG) und Voll-/Differentialblutbild beurteilt. Als immunpathologisches Nachweisverfahren dient das spezifische antikörpergekoppelte Nachweisverfahren ELISA (enzyme-linked immunosorbent assay) für humorale Antikörper gegen das rAAV8 Capsid-Protein, um die zelluläre Immunantwort gegen das rAAV8 Capsid-Protein zu überwachen. Die Biodistribution

[figure not shown]

3204 wird durch Polymerase-Kettenreaktion (PCR)-Untersuchungen über das rAAV8  
3205 Genom in Blut und Urin überwacht werden.

3206

3207 **Statistische Methoden:**

3208 Deskriptive Statistik ist geplant.

3209

3210 **Zeitplan:** Studienstart November 2015, Ende der Rekrutierung November 2016,  
3211 Studienende November 2017, Dauer der Studie pro Patient: ein Jahr mit  
3212 anschließend vier Jahren Nachbeobachtungsphase.

3213

3214

3215 **VII Flowchart of Visits and Procedures**

3216

3217 See next page

| Flowchart of Visits and Procedures CNGA3 Trial |                                                                   |               |     |    |    |         |          |          |          |          |                      |           |           |           |           |
|------------------------------------------------|-------------------------------------------------------------------|---------------|-----|----|----|---------|----------|----------|----------|----------|----------------------|-----------|-----------|-----------|-----------|
|                                                | Visit (no)                                                        | 1             | 2   | 3  | 4  | 5       | 6        | 7        | 8        | 9        | 10                   | Fup 1     | Fup2      | Fup3      | Fup 4     |
|                                                | Date                                                              | Screening     | D 0 | D1 | D2 | D3      | D14      | D30      | D90      | D180     | D365, Close out / ET | M24       | M36       | M48       | M60       |

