### 3.4. Number of enrolled patients

Nine patients will be enrolled in the trial. Drop-outs will only be replaced in case of non-ocular, non-treatment related reasons for the drop-out up to a number of two patients.

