### 7.4. Rules for discontinuation of the trial

Any of the following events will result in discontinuation of the trial:

5. Severe loss of vision (more than 15 letters ETDRS acuity) occurring deemed to be a result of vector administration.
6. Severe ocular, vector-induced inflammation, unresponsive to treatment (endophthalmitis).
7. Any suspected unexpected serious adverse reaction (SUSAR).
8. Safety concerns other than those mentioned under 1-3 and consecutive request for discontinuation by the Data Monitoring Committee.

If an Adverse Event was the reason for discontinuation of the trial either by the PI or the participant, the participant must undergo an early termination visit (see flowchart). The patient must be given appropriate care under medical supervision until symptoms cease or the condition becomes stable. Maximal follow-up duration will be 1 year after trial termination

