#### *10.2. Sample Size Issues*

No statistical sample size estimation was performed as no data are available regarding the safety of rAAV.hCNGA3 (first dose in man) or any other effect in the eye for such a calculation. As three vector dosages are planned in a dose-escalating schedule we decided for three patients in each group. Drop-outs will only be replaced up to a number of two patients in case that other reasons than vector- or procedure-related adverse events are the underlying reasons for the drop-out.

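### The early termination visit is mandatory only after an adverse event, so no final examination is required of an injected patient who leaves before D365 for another reason

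*Supplement*

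**What the plan says.** Section 7.4 of protocol version 5.0 lists the events that end the trial and then adds a rule on leaving early. The condition is "If an Adverse Event was the reason for discontinuation of the trial either by the PI or the participant"; the consequence is that "the participant must undergo an early termination visit (see flowchart").

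The flowchart (section VII) places this visit in the Visit 10 column, headed "D365, Close out / ET". The column marks acuity, fundoscopy, OCT, autofluorescence, ERG, vital signs, and haematology and chemistry as required. It does not say which leavers must attend.

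On numbers, section 3.4 states: "Nine patients will be enrolled in the trial". It continues: "Drop-outs will only be replaced in case of non-ocular, non-treatment related reasons for the drop-out up to a number of two patients". Section 10.2 words the replacement rule differently, allowing it "in case that other reasons than vector- or procedure-related adverse events are the underlying reasons for the drop-out". The same section says "No statistical sample size estimation was performed", and no drop-out rate is given anywhere.

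Section 10.3 keeps in the Safety Population every dosed subject with at least one safety assessment after therapy. Under 8.4.34, adverse events are elicited by open questions at each visit, covering the time since the previous one.

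**The concern.** The primary endpoint is safety, and its first ocular component in 7.2.1 is a loss of 15 or more letters, which can be seen only if acuity is measured. The protocol itself expects harm that may come late. Section 7.2.3 says that toxicity of the transgene product is unlikely to show in the first two weeks and may appear as worsening acuity after surgical recovery. Section 7.5 says that deterioration may follow an initial improvement, and its Table 2 predicts cataract in 10-20%.

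A rule triggered by a recognised adverse event works only when the event is already known. A patient who cites travel burden, or gives no reason, does not trigger the examination that could reveal an unnoticed change. Followed as written, the rule makes the presence of the final assessment depend on the reported reason for leaving. In a first-in-human trial of nine patients, each such gap is a sizeable share of the late safety evidence.

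**Working it through.** The plan states no figure on this point, so there is none to reproduce. The check is a comparison of passages followed by simple counts.

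**1. Who must have the visit**

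| Leaver (already injected) | ET visit required by 7.4? | Replaceable under 3.4 / 10.2? |
|---|---|---|
| Vector- or procedure-related adverse event | Yes | No |
| Unrelated, non-ocular adverse event | Yes | Yes, up to two |
| Non-ocular, treatment-unrelated reason that is not an adverse event | No requirement found | Yes, up to two |

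The third row is the gap. The replaceable group and the group without a required visit overlap but are not the same.

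**2. What the last required data would be** (flowchart, nominal days)

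| Last visit attended | Acuity | OCT, autofluorescence | ERG | Haematology, chemistry |
|---|---|---|---|---|
| D14 | D14 | D14 | screening | D14 |
| D30 | D30 | D30 | D30 | D14 |
| D90 | D90 | D30 | D30 | D14 |
| D180 | D180 | D30 | D30 | D180 |

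OCT and autofluorescence are optional at D90 and D180. ERG is blank at D90 in the flowchart (optional in 8.2) and optional at D180. After D30, these three become mandatory again only in the D365/ET column.

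An ET visit does not recover D365 values. It covers the time from the last assessment to departure. For someone leaving just before D365, that is up to 365 - 180 = 185 days for acuity and up to 365 - 30 = 335 days for required OCT, autofluorescence and ERG.

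**3. Ceiling on the patients affected**

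Inputs: 9 planned (3.4) and at most 2 replaced (3.4, 10.2). Assumptions: both drop-outs had been injected, and both left for reasons other than an adverse event.

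- With replacement: 9 + 2 = 11 injected; 2/11 = 18.2%.
- Two losses without replacement: 2/9 = 22.2%.
- One event missed: 1/11 = 9.1 or 1/9 = 11.1 percentage points on the crude rate.
- One loss within a dose cohort: 1/3 = 33%.

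**4. What this does to late safety evidence**

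With no events among n patients, the one-sided 95% upper bound is 1 - 0.05^(1/n):

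- n = 11: 23.8%
- n = 9: 28.3%
- n = 7: 34.8%

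Thus two incomplete patients raise the bound for late events from 28.3% to 34.8% (nine injected, seven complete), or from 23.8% to 28.3% (eleven injected, nine complete).

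The documents give no risk of a late event. For assumed risks of 5%, 10% and 20%, the chance of seeing at least one, 1 - (1 - p)^n, is 37%, 61% and 87% with nine patients and 30%, 52% and 79% with seven.

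**The case against.** The strongest reply is that the gap is narrow and partly covered.

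- **The rule does not forbid the visit.** Section 7.4 says if, not only if, and the flowchart column carries no restriction by reason. A reader might infer that patients who leave for other reasons contribute no close-out data. The documents do not support that; the visit is available but not required. This stands.
- **Replaced patients are not the same as unexamined patients.** A reader might infer that the drop-outs to be replaced are exactly those without a final visit. Someone who leaves for an unrelated systemic adverse event is replaceable and does trigger the visit. This stands.
- **Earlier data are not lost.** Acuity and fundoscopy are required at D14, D30, D90 and D180, and the Safety Population in 10.3 keeps dosed patients with at least one assessment after therapy. This stands, and it limits the loss to the period after the last assessment.
- **The definition of an adverse event in 7.2.3 is broad.** A patient who leaves because vision has worsened has an adverse event and falls under the present rule. This stands for complaints that are voiced. It does not help with a change that the patient has not noticed or reported.
- **Section 7.5 provides contact at least once a year.** This helps little. That contact is a questionnaire, not an examination, and is not stated to cover patients who withdrew.
- **Other papers may hold a withdrawal procedure.** The Procedure Manual and the contract research organisation's procedures are not shown, and the consent pages were removed. The absence can be asserted only for the text available.

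**Conclusion.** The point holds in limited form. In version 5.0 the only stated requirement for an early termination visit depends on an adverse event being the reason for leaving. The text shown contains no counterpart for an injected patient who leaves for another reason. The consequence is a final assessment that may be missing according to the reported reason; it is not the loss of the patient's safety record.

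The affected share is at most 18% (2 of 11) with both replacements, or 22% (2 of 9) if two leave and are not replaced. A reader might take these as expected losses. They are ceilings. Nothing in 3.4 or 10.2 limits replacement to patients already injected, so a replaced drop-out might never have received vector, and the reason might be an unrelated adverse event that does require the visit. The true frequency is unknown and could be zero. This is a cheap improvement to a small first-in-human safety trial, not a fault that undermines it.

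**What to change.** Amend the sentence in 7.4 so that every injected patient who stops before D365, for any reason, is asked to attend the ET visit in the D365/ET column of the flowchart. Word it as withdrawal of an individual participant, because the present sentence speaks of discontinuing the trial and sits among the rules for stopping it as a whole. The Safety Population definition in 10.3 already retains these patients and needs no change.

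The cost is one sentence, submitted as an amendment, and at most a few visits with assessments that are already defined. Patients remain free to decline, so the yield is uncertain. Recording refusals would at least show where final data are missing and why.

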#### **Treatment:**

Each cohort will receive a different, increasing dosage of viral vector genome particles. Three cohorts of patients are planned with low, medium and high dose administration levels up to  $1 \times 10^{11}$  of rAAV8 incorporating the therapeutic expression cassette.

After standard three-port 23G pars plana vitrectomy, balanced salt solution will be used to induce a localized primary retinal detachment in a controlled fashion. Vector solution will be applied using disposable 41G extendible subretinal injection needles within a standard 23G body to fit the port system. Administration will be unilateral (worse eye) in each patient.

**Primary Endpoint:** Safety as the primary endpoint will be assessed by clinical examination of ocular inflammation (slit lamp, fundus biomicroscopy, angiography, perimetry or electrophysiology). Systemic safety will be assessed by vital signs, routine clinical chemistry testing (including CRP, ESR) and full/differential blood counts. Immunopathology essays will include specific enzyme-linked immunosorbent assays for humoral antibodies against rAAV8 capsid protein. Biodistribution will be monitored by polymerase chain reaction studies on rAAV8 genome in blood, urine, saliva and lachrymal fluid.

**Statistical Methods:** AEs and SAEs will be documented using line listings and tabulations (MetraCad code will be applied). Descriptive analysis will include line charts for individual patients. Standard errors and means will also be displayed using line charts. This will be done for the raw measurements and for the difference between treated and untreated control eye within each patient.

Descriptive parameters will be given for the full cohort (n=9) but not for the sub-cohorts (n=3). Additionally correlation analysis will be performed in a purely descriptive manner for the comparison of subjective and objective measurements. For each subject and measurement, the delta of the value for the interventional eye minus the mean of control eye values over time will be determined. In scatter plots for pairs of variables (measurements pooled over subjects) the association between these deltas will be displayed.

**Time Schedule:** Start of trial November 2015, end of recruitment November 2016, end of trial November 2017, duration of trial per patient: one year with four years of follow-up.

[figure not shown]

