### 3.2. Study Duration

- First patient first visit: November 2015
- Last patient first visit: November 2016
- Last patient last visit: November 2017
- Duration of trial participation per patient: 1 year plus 4-year follow-up period

After five years a clinical routine visit once per year and/or questionnaire will be performed (see also section 7.5) for long-term follow-up.

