### 7.3. Reporting Procedures for all Adverse Events

All AEs occurring during the study observed by the investigator or reported by the participant, whether or not attributed to study medication, will be recorded on the CRF. The following information will be recorded: description, date of onset and end date, severity, assessment of relatedness to study medication, action taken and the outcome of AEs.

AEs considered related to the study medication as judged by a medically qualified investigator or the sponsor will be followed until resolution or the event is considered stable and/or until the end of the follow-up period (4 years).

The severity of events will be assessed on the following scale: 1 = mild, 2 = moderate, 3 = severe. The relationship of AEs to the study medication will be assessed by a medically qualified investigator and discussed with the PI.

[figure not shown]

Any *pregnancy* occurring during the clinical study and the outcome of the pregnancy of female patients or fathered by trial participants, should be recorded and followed up for congenital abnormality or birth defect until delivery. Pregnancy itself is documented as AE, in case of hospitalization as SAE.

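### Section 7.4 caps follow-up at one year after an undefined trial termination; after an early stop, this ends follow-up of an unresolved related event sooner than section 7.3 requires

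*Supplement*

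**What the plan says.** All references are to protocol version 5.0.

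- **Section 7.4** lists the events that stop the trial, among them "Severe ocular, vector-induced inflammation, unresponsive to treatment (endophthalmitis". It then covers discontinuation for an adverse event, opening with "If an Adverse Event was the reason for discontinuation of the trial either by the PI or the participant". Such a participant has an early termination visit. Next comes the care rule: "The patient must be given appropriate care under medical supervision until symptoms cease or the condition becomes stable". The section ends with "Maximal follow-up duration will be 1 year after trial termination". The text shown does not say what trial termination means.
- **Section 7.3** says that related adverse events "will be followed until resolution or the event is considered stable and/or until the end of the follow-up period (4 years". It has no exception for participants who have discontinued and does not mention the one-year limit. The items to be recorded include "action taken and the outcome of AEs".
- **Section 3.2** gives "Duration of trial participation per patient: 1 year plus 4-year follow-up period", then a yearly routine visit or questionnaire after year five.
- **Section 7.5** has all patients screened after close-out and contacted at least once a year.
- **The synopsis (Time Schedule)** has "end of trial November 2017, duration of trial per patient: one year with four years of follow-up".
- **The flowchart** puts early termination in the same column as the D365 close-out. It does not say whether a participant who terminates early goes on to M24, M36, M48 and M60.

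**The concern.** Sections 7.3 and 7.4 give different end points for the same follow-up, and neither cites the other. A related event that is neither resolved nor stable one year after an early stop has met none of the end points in 7.3, so the and/or in that section does not reconcile them. Under 7.3 follow-up continues; under 7.4 it stops.

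The affected patients are the ones whose late course matters most. One of 7.4's own stopping events is inflammation that does not respond to treatment, which could plausibly still be active after a year. Safety is the primary endpoint, there are nine patients, and this is the first use of the vector in humans. Each affected patient is 1 of 9 (11%) of the evidence. That figure is the weight of one patient, not an estimate of how often this would happen.

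**Working it through.** The plan gives no figure to reproduce, so the check is a comparison of texts plus date arithmetic.

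**Inputs**
- End point in 7.3: the end of the 4-year follow-up. Section 3.2 places those four years after the first year, and the flowchart's last visit is M60, so the outer limit is month 60.
- Cap in 7.4: termination month + 12.
- Visit times in months: D30 = 1, D90 = 3, D180 = 6, D365 = 12.

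**Formulas** for a stop at month s: cap = s + 12, and shortfall = max(0, 60 − cap). The shortfall arises only if the event is related and still neither resolved nor stable when the cap is reached; otherwise it is 0. The last column counts the visits among M24, M36, M48 and M60 that fall after the cap, with a visit on the cap counted as kept. It applies only if the cap limits the participant's whole follow-up.

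| Stop at | s | Cap (month) | Shortfall against 7.3 (months) | Scheduled visits after the cap |
|---|---|---|---|---|
| D30 | 1 | 13 | 47 | 4 |
| D90 | 3 | 15 | 45 | 4 |
| D180 | 6 | 18 | 42 | 4 |
| D365 | 12 | 24 | 36 | 3 |
| M24 | 24 | 36 | 24 | 2 |
| M36 | 36 | 48 | 12 | 1 |
| M48 | 48 | 60 | 0 | 0 |
| M60 | 60 | 72 | 0 | 0 |

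The shortfall disappears when s + 12 ≥ 60, that is, from s = 48.

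**Other meanings of trial termination**
- *Planned end of trial, November 2017.* The cap is November 2018. For the first patient (first visit November 2015) that is about M36, a shortfall of 60 − 36 = 24 months. For the last patient (first visit November 2016) it is about M24, a shortfall of 60 − 24 = 36 months.
- *End of the five-year participation.* The cap is month 72, after the end of 7.3's period, so the shortfall is 0.

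**Scope of the cap**
- *Only the event that caused the stop.* The conflict is with 7.3 alone, within the limits above.
- *The participant's whole follow-up.* The cap would then also conflict with 3.2 (1 plus 4 years, then yearly) and with 7.5 (all patients, at least yearly contact).

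**The case against.** The strongest reply is that 7.3 is the general rule and 7.4 a specific one for participants who stopped because of an adverse event, so the cap can be read as a deliberate exception. That is possible, but nothing in the text says so, and the exception would shorten follow-up for the patients with the most serious events. An intended exception would need its start and scope stated, and both are missing.

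A second reply is that several conditions must coincide: an adverse event that caused discontinuation, judged related, still unstable a year later, after a stop early enough to matter, in someone who has not withdrawn consent. A fixed visual loss would count as stable under both sections. This stands, and it is why the severity is modest. The documents give no rate for such cases.

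A third is that information need not stop at the cap. An outcome of not resolved can be recorded then, and the yearly questionnaire in 7.5 asks about adverse events and visual disturbances. That also stands if the cap covers only the causal event, though a questionnaire does not replace an examination.

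A reader might also infer that 7.4 contradicts itself, because care until stable is followed by a one-year maximum. The documents do not establish this. The second sentence may simply limit the first, or clinical care may continue outside the trial after study follow-up ends. It is an ambiguity to clear up.

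**Conclusion.** The point holds: the follow-up rule in 7.4 is inconsistent with 7.3 as written, with modest severity. For a related event still unstable a year after an early termination, the shortfall runs from 47 months (stop at D30) to 12 months (stop at M36). If termination means the planned end of trial, it is 24 to 36 months. It is zero if the event resolves or stabilises within the year, if the stop is at M48 or later, or if termination means the end of the five-year participation. What is affected is the completeness of primary safety data and the surveillance of the patients concerned.

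Two stronger inferences go too far. One is that 7.3 and 7.4 clash whatever the timing; the conflict needs termination before about month 48. The other is that participants who discontinue for an adverse event lose their M24 to M60 visits. That follows only if the cap limits all follow-up. Nothing in 7.4 cancels those visits, and the all-patients wording of 7.5 speaks against that reading, although version 5.0 does not settle the matter.

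The result rests on taking month 60 as the outer limit in 7.3 and on the absence of any precedence rule in the text shown.

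**What to change.** Delete the one-year sentence in 7.4 and put two statements in its place:

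1. Adverse events judged related are followed as set out in 7.3, including after discontinuation.
2. Treated participants who discontinue because of an adverse event have the early termination visit and then continue the M24 to M60 visits and the yearly contact of 3.2 and 7.5, unless they withdraw consent.

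If the sponsor wishes to keep a time limit, 7.4 should define when it starts, say whether it covers the causal event or all follow-up, and exempt related events that are neither resolved nor stable.

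The cost is one sentence removed and two added. No new type of visit or test is needed, because the M24 to M60 schedule and yearly contact already exist. The downside is that the few affected patients keep visits that the cap, on its widest reading, would have spared them. Under section 13 the change also needs an amendment, with a revised patient information form signed by all patients.
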